#### Treatment as usual

For TAU, usual procedures at the site will be followed in which the optimal treatment for the specific patient is chosen by experienced clinicians. No restrictions except for schema therapy with experiential elements are made for the TAU-condition. In this way, TAU mimics usual practice. Offered treatments for this study include Affect Phobia Therapy (AFT; individual or group), Cognitive Behavioural Therapy (CGT; part- or fulltime), Psychodynamic psychotherapy (individual or group), Guideline-Informed Treatment for Personality Disorders (GITPD), Short-term Schema Cognitive–Behavioural Group Therapy (SCBT-g [32];), or treatment by a psychiatric nurse. Although SCBT-g is sometimes viewed as a form of ST, we deemed it sufficiently different from ST delivered in the GST protocol because of its predominant use of cognitive techniques and its focus on the present. Importantly, experiential techniques and the specific use of the groups dynamics characteristic of GST are not part of the SCBT-g protocol.

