##### Analyses

All analyses are planned to be carried out by SPSS or R statistical software and Excel (for Bootstraps).

Primary and secondary outcomes are analysed with Linear Mixed Models (LMM), with random effect of site. As data of group members are not independent because group members might influence each other, this dependency needs to be taken into account. With the semi-closed group format, groups change in composition every 10 sessions, and participants will share different amounts of time in sessions with group peers: from all group sessions to 10 group sessions. It is plausible to model covariances as a function of the amount of time (i.e., sessions) patients have spent together in a group. This can be achieved in a multilevel model with repeated measures by specifying a Toeplitz covariance structure to model this dependency on the group level. In case this Toeplitz structure turns out to be unsuitable to model the dependency, another (less complex) structure will be specified. For the repeated part at the individual level, the best fitting covariance structure will be chosen (e.g., AR1, ARMA11, Unstructured). If residuals deviate substantially from normal distribution, Generalized LMM (GLMM) will be used with an appropriate distribution (e.g., negative binomial or gamma in case of skewed distributions). All analyses are conducted on the basis of intention-to-treat and will be controlled for initial symptom severity. Dropout from treatment will be analysed with GLMM survival analysis with site as random effect. To take into account participants’ potential influence on each other in group treatment, again a Toeplitz covariance structure will be specified to model this dependency unless a different structure turns out to be more suitable. The three arms will be mutually compared, with a primary interest in the GST-TAU and the GST-IST comparisons. Although the IST-TAU difference is not part of the main research questions, this difference will be analysed exploratively. Tests of predictors and moderators (sleep quality, introversion, autism traits, childhood trauma, verbal intelligence, demographic characteristics) will be done by similar (G)LMM analyses, with the predictor, predictor x time, predictor x treatment, and predictor x time x treatment interactions added to the model.

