To derive a tool that informs future patients and therapists what treatment is likely to be most efficacious for the specific patient (personalized care), we currently plan to use the Personalized Advantage Index (PAI) procedure developed by DeRubeis [61]. The LMM model of the outcome analysis is the starting point. Then, potential predictors and moderators are derived by suitable predictive machine learning models. Two methods for model selection, best subset selection and Lasso regression, will be performed and validated using 10-fold cross validation, after which one of the two methods will be selected. The individual’s PAI and hence the advantage of optimal treatment allocation can be estimated with a leave-one-out procedure [61, 62]. However, the field of personalized treatment allocation is developing rapidly and other methods might turn out to be more accurate and robust than the PAI method. We will therefore use a method that is optimal given the state of affairs at the end of data collection.

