Naturally, a clinical, multicenter RCT involves complex decisions to ensure the quality and feasibility of the trial. Here we outline some of these key considerations and challenges. Firstly, as TAU will be the primary treatment offered to the individual patient at each participating site, TAU reflects the current optimal clinical practice in the Netherlands. The variety of TAU types over the 10 sites spread over the Netherlands is meant to be representative of the current usual treatment of Cluster-C PDs in clinical practice. A downside to not formulating guidelines for the TAU is that little control can be executed over treatment-specific variables that are more fixedly regulated in the IST and GST conditions (e.g., frequency and intensity of treatment, therapist training and supervision). Nevertheless, protocolized treatments like Affect Phobia Therapy and SCBT-g are currently quite common in Dutch mental health care and are usually given by trained therapists. To document the TAU provided, questionnaires are administered to register treatment as well as therapist characteristics that can be entered into later analysis.

Next to the advantages of conducting research in multiple mental health centers regarding generalizability, it also introduces potential bias of characteristics related to sites rather than treatments (different location, patient demographics, therapists, etc.). These non-treatment specific variables can differentially influence treatment outcomes and can complicate the interpretation of the results (hence reducing generalizability). We therefore will use multilevel analysis that takes this structure of the data into account. Multilevel analysis allows for modelling variance at the site-level and differentiating treatment-specific from site-specific influences.

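### Moderator tests against TAU name a site effect but no site-by-treatment term, so site differences in TAU can leak modestly into the predictor-by-treatment effect

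*Protocol article*

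**What the plan says.** All references are to the Protocol article.

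- **Outcome model** (Analyses): "Primary and secondary outcomes are analysed with Linear Mixed Models (LMM), with random effect of site". The other dependence terms are a Toeplitz structure for shared group sessions and a covariance structure for repeated measures.
- **Moderators** (Analyses): the tests "will be done by similar (G)LMM analyses, with the predictor, predictor x time, predictor x treatment, and predictor x time x treatment interactions added". None of these four terms involves site, and the predictor is not split into within-site and between-site parts.
- **Tool** (Analyses): "The LMM model of the outcome analysis is the starting point". Model selection is "validated using 10-fold cross validation", and for the individual index "the advantage of optimal treatment allocation can be estimated with a leave-one-out procedure". No split by site is mentioned. The method is provisional and may be replaced once data collection ends.
- **TAU** (Treatment as usual): "usual procedures at the site will be followed in which the optimal treatment for the specific patient is chosen by experienced clinicians". The Discussion adds that the types of TAU vary over the 10 sites.
- **Site differences** (Discussion): location, patient demographics and therapists are named as possible sources of bias. "These non-treatment specific variables can differentially influence treatment outcomes and can complicate the interpretation of the results (hence reducing generalizability"). The remedy offered is multilevel analysis with site-level variance, which is said to separate treatment influences from site influences.

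**The concern.** A random intercept for site absorbs differences in average outcome. It does not absorb a treatment effect that is larger at one site than at another. Randomisation within site protects the main GST-TAU and GST-IST contrasts, but a patient characteristic is not randomised. When a predictor's mean differs between sites, its interaction with treatment pools two things:

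- the within-site interaction, which is protected by randomisation and is the quantity wanted;
- the between-site association of the site's TAU effect with the site's patient mix, which is not protected.

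If sites with a weaker TAU also happened to have patients with less education, education could look like a moderator without being one. This bears on the third main question, which characteristics predict better response to which treatment, and on the tool, which is meant for future patients. Cross-validation that leaves out patients keeps others from the same site, under the same local procedures, in the training data. It therefore says little about performance at a new site.

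**Working it through.** **1. The protocol's own figure.** Sample size gives 90% power for 162 versus 108 patients, d = 0.44, p-level 0.025. SE = √(1/162 + 1/108) = 0.1242; 0.44/0.1242 = 3.542; two-sided critical value 2.241; power = Φ(3.542 − 2.241) = 0.903 (0.900 with the noncentral t). It reproduces. No figure is given for the moderator tests.

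**2. Inputs from the protocol.** Nine sites (the basis of the power calculation). Per site: 162/9 = 18 GST, 108/9 = 12 IST, 108/9 = 12 TAU. The assumed TAU contrast is 0.44.

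**3. Inputs assumed, because the protocol does not give them.** Residual SD 1, site intercept SD 0.2, predictor slope 0.2, no true moderation, one outcome time point. Varied: the SD τ of the TAU effect between sites (0 to 0.44), the share of predictor variance between sites (ICC, 2% to 20%), and the correlation ρ of site TAU effect with site predictor mean (0 to 1).

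**4. Expected spurious interaction.** With predictor SD 1, the site mean has SD √ICC. Regressing the site TAU effect on it gives slope ρτ/√ICC. The between-site part has weight of about ICC in the pooled interaction, so the bias is about ρ·τ·√ICC:

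- ρ = 0.5, τ = 0.3, ICC = 0.1: 0.5 × 0.3 × 0.316 = 0.047 (simulated 0.049)
- ρ = 0.5, τ = 0.44, ICC = 0.1: 0.5 × 0.44 × 0.316 = 0.070 (simulated 0.061)

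**5. Simulated type I error, predictor × TAU versus GST, two-sided 5%.** Three arms, generalised least squares, 1,500 runs per row. The Monte Carlo SE is √(0.05 × 0.95/1500) = 0.6 points at 5% and √(0.107 × 0.893/1500) = 0.8 points at 10.7%.

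| τ | ICC | ρ | Site intercept only | Mean spurious slope | Site × TAU slope plus within-site predictor |
|---|---|---|---|---|---|
| 0 | 10% | 0 | 4.5% | −0.001 | 4.3% |
| 0.2 | 10% | 0 | 5.3% | −0.001 | 4.7% |
| 0.3 | 10% | 0 | 6.2% | 0.001 | 4.8% |
| 0.44 | 10% | 0 | 7.3% | 0.004 | 4.9% |
| 0.2 | 10% | 0.5 | 5.9% | 0.026 | 5.2% |
| 0.3 | 10% | 0.5 | 8.1% | 0.049 | 4.4% |
| 0.44 | 10% | 0.5 | 10.7% | 0.061 | 5.3% |
| 0.44 | 2% | 0.5 | 6.5% | 0.027 | 5.3% |
| 0.44 | 20% | 0.5 | 15.0% | 0.091 | 5.4% |
| 0.44 | 20% | 1 | 31.3% | 0.176 | 4.7% |

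A two-arm check with fixed site terms (ICC 10%, τ 0.3 and 0.44) gave 6.4% and 6.4% at ρ = 0, and 6.4% and 8.8% at ρ = 0.5. Fixed site × treatment terms brought these four to between 4.4% and 5.6%.

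**6. GST versus IST.** With only TAU varying by site, the corresponding interaction test stayed between 4.3% and 5.8%.

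**7. Is a correlation of 0.5 far-fetched?** If the two site quantities are truly unrelated, a sample correlation beyond ±0.5 arises by chance with probability 17% for 9 sites and 14% for 10. The ρ = 0 rows already average over such chance alignments.

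**8. A random site × TAU slope alone** gave 4.5% to 6.7%, with one exception of 8.9% (τ 0.44, ICC 20%, ρ 1), and left a bias of up to 0.07. It helps, but does not fully separate the two parts.

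**The case against.** The strongest reply is that the text does not say what the concern needs it to say. It names a random effect of site, and nothing rules out a site-by-treatment slope. The Sample size section mentions numerous random effects without listing them. A condensed article may leave slopes, centring and fold construction to a fuller document. This stands in part: a reader might infer that the model holds a site intercept and nothing else, and the protocol does not establish that. What remains is that the Discussion presents the multilevel model as separating site from treatment influences. The site term as named does not do this for interactions unless it is more than an intercept, and even a random slope leaves some bias.

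Other points also stand:

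- Site differences in patient mix are described as possible, not as observed. TAU is chosen per patient within a site, so a single site TAU is a simplification.
- TAU and therapist characteristics are recorded and may enter later analyses. That is relevant, but optional and tied to no moderator model.
- The tool method is provisional, so its validation is not fixed. The section This study says the tool rests on an empirically derived subset, so a reader should not infer that ethnic background, socio-economic status and education will all enter it.
- Every site-level input is assumed. Rates of about 20% to 31% need a perfect correlation and τ = 0.44, a between-site SD as large as the whole planned effect. They should not be read as expected.
- Extending the concern to GST-IST would need GST or IST effects that themselves vary by site. Both follow protocols with training requirements, and the calculation does not show it.

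**Conclusion.** The concern holds in a limited form. As written, the moderator tests and the tool's starting model include site but no site-by-treatment term, while TAU is acknowledged to vary over sites. If the site effect is an intercept, the remedy in the Discussion does not protect predictor-by-treatment in contrasts with TAU.

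With 10% of predictor variance between sites, type I error is about 5 to 7% when site TAU effect and patient mix are unrelated. At a correlation of 0.5 and a TAU SD of 0.3 to 0.44 it is about 7 to 11%, the lowest cell of the two-arm check being 6.4%. For predictors spread evenly over sites the effect is smaller. A reader might go further and infer that the randomised main comparisons are compromised. They are not: allocation is made within site. This is a modest improvement to a secondary but stated aim, not a flaw that threatens the trial.

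**What to change.** 1. In moderator models for contrasts with TAU, add site × treatment terms, or centre the tested predictor at its site mean. State that moderation is read from the within-site interaction. If a random slope is preferred, combine it with centring.
2. Whatever tool method is finally chosen, report its performance with whole sites left out, next to the patient-level cross-validation. Adding site means and their interactions for about ten candidates over about ten sites is not practical in the tool and is not asked for.
3. State which site-level random effects the outcome model contains.

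**Cost.** The standard error of the within-site interaction grows by about 1/√(1 − ICC): 1/√0.9 = 1.05 and 1/√0.8 = 1.12, that is 5% to 12% for ICC 0.1 to 0.2. There is slightly more analysis work and no change to data collection or sample size.

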A popular and economically attractive form of ST is group treatment, as larger numbers can be treated in less therapist time than with individual therapy (>50%), making it potentially more cost-effective than IST. In addition, the group format might offer extra therapeutic advantages such as support and understanding from group members which can help patients gain a sense of belonging and can facilitate secure attachment. Possibly group therapy would be exposure in itself for patients with cluster-c PD, where social avoidance and dependence play a major role in their pattern of symptoms. Furthermore, group therapy can induce vicarious learning and offer in vivo opportunities to practice with setting boundaries and expressing one's needs in a healthy way [16]. Group schema therapy (GST) has proven to be an effective treatment for borderline PD [17, 18] and was found superior to TAU [19, 20]. Only two studies have investigated GST for Cluster-C PD. First, a modest pilot study of a GST-protocol including 8 patients with mixed personality disorders (6 patients with avoidant PD and 2 with borderline PD) showed significant decline in avoidant PD symptom severity at follow-up [21]. The two patients with borderline PD were both reported as dropout, suggesting that mixing different PDs within this GST-protocol may be contra indicative. Second, a larger pilot study investigated our current GST-protocol in a multicenter open trial (9 sites, 137 patients). The treatment was highly acceptable: only 16 dropouts (11.6%). The decrease in symptoms from baseline to follow-up of the primary PD was large (effect sizes ranged from cohen’s d = .59 for obsessive compulsive PD, d = 1.33 for avoidant PD and, d = 1.52 for dependent PD).

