### This study

This paper describes the QUEST-CLC study (QUalitative and Effectiveness study to Select optimal Treatment for CLuster-C PD), a multicenter RCT comparing GST, IST, and TAU for Cluster-C PDs. The main objective of the study is to compare the relative (cost-) effectiveness of these three treatments. Based on previous research, superiority of GST to TAU is expected regarding PD symptom reduction. How GST compares to IST in (cost-) effectiveness is yet unclear. Although in GST larger numbers can be treated in less therapist time than with IST, it is not yet clear how this relates to respective treatment effects. It is hypothesized that GST does not perform worse than IST regarding symptom reduction. As the few previous studies on treatment for Cluster-C PDs that do exist are generally limited to symptom reduction, measures of quality of life, social, work, and other functioning are also included. Furthermore, this study intends to identify predictors and moderators that are relevant for optimal treatment allocation. With such moderators a tool for treatment recommendation will be created. The tool is based on an empirically derived subset of several variables hypothesized to correlate with therapy outcome (i.e., diagnoses, age, gender, ethnic background, socio-economic status, educational level; introversion, autistic traits, sleep problems, severity of childhood traumas).

In addition, two sub studies will be carried out. First, the treatment integrity of GST and IST will be evaluated and compared with TAU. Second, a qualitative study will be performed in which patients and therapists are interviewed. The aim is to obtain a thorough understanding of how the different therapies helped patients recover, what elements are pivotal to lead a fulfilling life, and to explore experiences for patients in the ST-arms, in order to improve ST for Cluster-C patients. Moreover, ST-therapists’ perspectives about treatment will be used to further improve treatment protocols (as was done in the pilot study [24, 25]).

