##### Introversion

To assess introversion, the authors have developed a questionnaire due to lack of short and open-source instruments that focus on characteristics of introversion rather than the absence of the trait extraversion. The ‘Introversion Inventory’ [53] is based on the Big-5 Facet theory underlying the NEO-PI-R ([54] extraversion scale. The Introversion Inventory has 19 items with answering options ranging from 0 (completely incorrect) to 4 (completely correct). A (translated) example question is ‘In company I am reserved’. This new scale will be validated in this and adjacent studies and made available as an open-source instrument. Although introversion is hypothesized to be a predictor, this questionnaire was also added to the repeated measurements to see if changes occur over time due to influences of (group) therapy.

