#### Predictors-moderators

##### Autism Characteristics

The Dutch Autism-Spectrum Quotient-10 (AQ-10 [55]; is used to measure autism characteristics. The AQ-10 consists of 10 items scores on a 4-point Likert scale, determining one’s difficulties with social skills, routine, imagination, detail-focus, and attention switching. The total score ranges from 0-10, with a higher score indicating more autistics traits. A score of 6 or higher is indicative for a full diagnostic assessment [56]. The internal consistency of the AQ-10’s total score is high (α = .85 [57];). The AQ-10 is able to distinguish between individuals with and without a clinical diagnosis of ASD [56].

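### As written, the introversion and AQ-10 moderator tests cannot show that the trait itself, rather than primary diagnosis or severity, drives a treatment difference

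*Protocol article*

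**What the plan says.** The Analyses section of the protocol article names the moderators: "Tests of predictors and moderators (sleep quality, introversion, autism traits, childhood trauma, verbal intelligence, demographic characteristics) will be done by similar (G)LMM analyses". Primary diagnosis is not in that list. The section then writes out the model terms, as the outcome model "with the predictor, predictor x time, predictor x treatment, and predictor x time x treatment interactions added to the model". It also says that all analyses "will be controlled for initial symptom severity"; it states no interaction of severity with treatment or time.

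Elsewhere diagnosis does count as a candidate. The section headed This study gives the variables for the treatment-recommendation tool as "diagnoses, age, gender, ethnic background, socio-economic status, educational level; introversion, autistic traits, sleep problems, severity of childhood traumas", and the Discussion says that the authors want to know whether the recommendation differs by primary diagnosis. The tool has its own procedure: "Two methods for model selection, best subset selection and Lasso regression, will be performed and validated using 10-fold cross validation".

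On the instruments, the Introversion section says: "A (translated) example question is ‘In company I am reserved’. This new scale will be validated in this and adjacent studies". The AQ-10 is described as "determining one’s difficulties with social skills, routine, imagination, detail-focus, and attention switching". The Background suggests that group therapy may be "exposure in itself for patients with cluster-c PD, where social avoidance and dependence play a major role in their pattern of symptoms", and it lists avoidance and excessive control as typical Cluster-C coping.

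**The concern.** The Background gives mechanisms for its moderator hypotheses. Introverted patients may be less suited to a format built on sharing, and autistic features may make group processes hard to follow, so IST might serve such patients better. These are claims about the traits themselves.

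The questionnaire content resembles the disorders under treatment. Social reserve is also what a patient with avoidant PD would be expected to report. Difficulty with social skills, attachment to routine and a focus on detail sit close to avoidant and obsessive-compulsive features. In this sample the scores may therefore partly reflect which PD the patient has and how severe it is.

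If the GST-IST difference varies with diagnosis or severity, a correlated trait picks up part of that variation. Controlling severity as a main effect does not prevent this, because the missing term is an interaction with treatment. The trial could then report that introverted patients do better in one arm when the operative factor is a diagnosis that the clinician already knows.

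**Working it through.** **The plan's own figure.** Sample size gives 90% power for d = 0.44 at p = .025 with 162 and 108 patients. SE = sqrt(1/162 + 1/108) = 0.1242, and 0.44/0.1242 = 3.542. The two-sided critical value is 2.241, and Φ(3.542 − 2.241) = 0.903 (0.900 with the noncentral t). The figure reproduces. It concerns arm comparisons and says nothing about moderators.

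**Inputs for the check.**
- From the protocol: arm sizes of 162 (GST) and 108 (IST); an outcome scaled so that SD = 1.
- Assumed, because the protocol gives no values: correlation ρ between the trait M and the true moderator D (diagnosis as two equal halves, or continuous severity), from 0 to 0.7; true D x treatment effect β of 0, 0.22 or 0.44 SD per SD of D.
- M has no moderating effect of its own. The test is two-sided at 5%, with 3,000 simulated trials per setting.

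For two equal diagnosis halves, one SD of D is half the distance between the groups. So β = 0.22 means that the GST-IST difference differs by 0.44 SD between diagnoses, and β = 0.44 means 0.88 SD. The second is twice the whole GST-TAU effect the trial is powered for, so it is a high setting.

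**Expected coefficient.** When D x treatment is left out, M x treatment estimates ρ × β whether or not D is present as a main effect. For ρ = 0.5 and β = 0.44 this is 0.220; the simulated means were 0.220 (diagnosis) and 0.225 (severity).

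**Hand check of rejection.** With M at unit variance, the SE of M x treatment is about 1/sqrt(270 × 0.6 × 0.4) = 0.1242. For ρ = 0.5 and β = 0.44, 0.220/0.1242 = 1.771 and Φ(1.771 − 1.960) = 0.425. The simulation gave 0.404 and 0.428.

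**Simulated share of trials that flag M x treatment** (diagnosis / severity as D):

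| ρ | β | D as main effect only | D x treatment added |
|---|---|---|---|
| 0.3 | 0.22 | 8.1% / 8.4% | 4.6% / 5.1% |
| 0.3 | 0.44 | 18.3% / 19.0% | 5.6% / 4.9% |
| 0.5 | 0.22 | 14.3% / 12.5% | 5.0% / 5.0% |
| 0.5 | 0.44 | 40.4% / 42.8% | 5.2% / 4.6% |
| 0.7 | 0.22 | 22.7% / 23.0% | 4.6% / 5.0% |
| 0.7 | 0.44 | 67.8% / 67.5% | 4.8% / 5.3% |

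With ρ = 0 or β = 0, every model rejects in about 5% of trials. Overlap alone does no harm; diagnosis or severity must also modify the arm difference.

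**Price of adjustment.** The SE of M x treatment grows by 1/sqrt(1 − ρ²): 1/sqrt(0.91) = 1.05, 1/sqrt(0.75) = 1.15 and 1/sqrt(0.51) = 1.40 for ρ = 0.3, 0.5 and 0.7.

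The simulation uses one time point and no site or group clustering. It shows direction and range, not rates for this trial.

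**The case against.** The strongest reply is that the planned test answers the question the trial asks. The abstract asks which characteristics predict better response. If introversion correlates with a diagnosis that modifies the treatment effect, introversion is a genuine marginal moderator and rejecting is correct. This stands. The rates above are errors only for the trait-specific reading, which the Background does put forward.

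A reader might also infer that a misattributed effect would be built into the allocation tool. The document does not support that. The tool is developed by best subset or Lasso selection over candidates that include diagnoses as well as both traits. That selection serves prediction, however; it is not a reported test of whether a trait adds to diagnosis and severity.

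A reader might infer that predictors are tested strictly one at a time. The singular wording suggests this but does not say it. Even if the listed predictors were entered together, primary diagnosis and the severity interaction would still be absent from what is stated.

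The pilot effects by diagnosis (d = .59 to 1.52) might be read as evidence of the required interaction. They are single-arm pre-post changes and do not show how GST-IST differs by diagnosis. The evidence for overlap is likewise limited to item and domain descriptions. Validation of the introversion scale is also planned outside this sample.

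One could say that a condensed article leaves covariate detail to the analysis plan. Here, though, the moderator list and model terms are written out, and the list departs from the article's own interest in diagnosis. Balancing randomization on diagnosis protects the arm comparison, not the attribution of a moderator.

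Finally, the adjusted model is large. With three arms and four post-baseline occasions treated as categories, two diagnosis contrasts and severity bring about 3 × (1 + 2 + 3 + 6) = 36 fixed effects, of which the severity main effect is already planned. If trait and disorder truly share content, adjustment may also remove part of the trait. This argues for reporting both models rather than replacing the planned one.

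**Conclusion.** The point holds in a limited form. A significant introversion or AQ-10 moderator from the model as stated would not establish that the trait itself matters beyond diagnosis and severity. The moderator list omits primary diagnosis although other sections of the article name it, and severity is stated only as a control.

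The magnitude cannot be fixed from the document. It ranges from none, if diagnosis and severity do not modify the GST-IST difference, to about 8% to 23% flagged at β = 0.22 and about 18% to 68% at β = 0.44, for assumed correlations of 0.3 to 0.7. The use of these tests for prediction, the construction of the tool and the primary arm comparisons are not called into question.

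**What to change.** - Add primary diagnosis to the moderator list in the Analyses section.
- For introversion and AQ-10, fit a second model that also contains primary diagnosis and baseline severity, each with its treatment, time and treatment x time interactions.
- Report it beside the planned model, together with the baseline correlations of each trait with diagnosis and severity.
- Limit any statement that a trait adds information beyond diagnosis and severity to the adjusted result, and present the planned result as predictive.
- State whether the listed moderators are tested singly or jointly.

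This changes analysis wording only, since the variables are already collected at screening or baseline. The statistical cost is a wider interval for the trait interaction: SE x1.05 to x1.15 at correlations of 0.3 to 0.5, and x1.40 at 0.7, before allowing for the extra time-by-treatment terms.
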